## **Clinical Laboratory Tests**

Blood samples for serum chemistry and hematology should be collected at the screening visit and at the time points listed in the Time and Events Schedule to assess clinically significant laboratory abnormalities. The investigator must review the laboratory reports, document these reviews, and record clinically important changes, whether serious or non-serious, which meet the adverse event reporting requirements as detailed in Section 12.3.1, in the adverse event section of the CRF.

The following tests should be performed by the local laboratory:

- Hematology Panel
  - hemoglobin
  - white blood cell (WBC) count with differential
  - platelet count
- Serum Chemistry Panel

|                                   |                                  |
|-----------------------------------|----------------------------------|
| -sodium                           | -gamma-glutamyltransferase (GGT) |
| -potassium                        | -bilirubin                       |
| -magnesium                        | -alkaline phosphatase            |
| -creatinine                       | -uric acid                       |
| -glucose                          | -calcium                         |
| -aspartate aminotransferase (AST) | -albumin                         |
| -alanine aminotransferase (ALT)   |                                  |
- Thyroid-stimulating hormone (TSH) test is required at screening and Weeks 4 and 8. Additional TSH tests should be performed at the recommended time points (eg, Weeks 12, 24, 48, and at the posttreatment follow-up visit) or according to local regulations, as per the standard-of-care, as presented in the Time and Events Schedule.
- Serum or urine pregnancy testing for women of childbearing potential only. A serum ( $\beta$ -HCG) pregnancy test is required at the screening visit and a serum or urine pregnancy test is required before first dose of treatment to ensure that the women are not pregnant at the time of starting treatment. For male subjects with female partners of childbearing potential, pregnancy tests are strongly recommended. See Section 4.3, Prohibitions and Restrictions, for additional information on pregnancy testing.
- Serology (HIV antibody, hepatitis B surface antigen [HbsAg], if not performed in the past or subject to change at screening)

### **Electrocardiogram**

An electrocardiogram (ECG) is recommended at the screening visit to assess clinically significant ECG abnormalities.

### **Vital Signs**

Pulse and blood pressure should be measured at the screening visit and at all visits in the open-label treatment phase.

### **Physical Examination**

Height should be measured at screening only, and weight should be measured at screening and all visits in the open-label treatment phase.

A complete physical examination should be performed at screening and should include a review of the following systems: head/neck/thyroid, eyes/ears/nose/throat, chest, lungs, heart, lymph nodes, abdomen, skin, musculoskeletal systems, and neurological systems. Other body systems (ie, anorectal, genital) should be examined if medically indicated. The screening physical examination should also include an eye examination, as per standard-of-care for Peg-IFN-alfa.

At all other visits up to 30 days after the last dose of telaprevir, physical examinations should be directed at detecting adverse events. Only those signs and symptoms that represent clinically important changes, whether serious or non-serious, meeting the criteria for reporting of adverse events in this early access program as described in Section 12.3.1, All Adverse Events, will be recorded in the CRF.

All physical examinations performed more than 30 days after the last dose of telaprevir should be completed according to clinical practice.

### **9.3.1. Specific Toxicities**

#### **9.3.1.1. Assessment, Treatment, Management, and Documentation of Rash**

Management of rash throughout the treatment period of the early access program should always follow generally accepted medical standards. In addition, the procedures described in the following paragraphs for the assessment, treatment, and management of rash cases should be followed.

Subjects will be instructed to contact the site immediately upon noticing a skin reaction and should be evaluated in a timely manner.

##### **9.3.1.1.1. Rash Assessment: Severity Grading**

Rashes will not be graded according to the DAIDS scale; instead the grade and severity of rash events should be assigned using the criteria described in the remainder of this section. If there is any doubt about severity grading of a rash event, the investigator must consult with the monitor before taking any action.

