**For rash, all grades will be recorded on the rash pages in the CRF.**

**Grade 1, mild:** Rash is defined as a localized skin eruption and/or a skin eruption with a limited distribution (eg, up to several isolated sites on the body), with or without associated pruritus. A mild rash will have no target lesions, no signs of systemic involvement, and no involvement of mucous membranes or signs of epidermal detachment.

**Grade 2, moderate:** Rash is defined as a diffuse skin eruption involving up to approximately 50% of the body surface area, with or without superficial skin peeling and/or pruritus. Mucosal inflammation without ulceration may be present. Note that mucosal conditions that are not related to skin events, such as aphthous ulcers, stomatitis, or oral lichen planus, should be well documented and not considered when the rash is graded. A moderate rash will have no target lesions or signs of epidermal detachment. Moderate systemic signs and symptoms, such as fever, joint pain, and/or eosinophilia, can be experienced with moderate morbilliform rash. Therefore the type of rash and a thorough assessment of the degree of any systemic signs and their temporal relation to the onset and/or its progression are necessary for rash grading.

**Grade 3, severe:** Rash is defined as a generalized rash involving over 50% of the body surface area, or rash presenting with any of the following characteristics:

- rash with vesicles or bullae;
- superficial ulceration of mucous membranes;
- epidermal detachment (full thickness epidermal necrosis and separation of epidermis from underlying dermis);
- atypical or typical target lesions;
- palpable purpura/non-blanching erythema;
- diagnosis of drug-related eosinophilia with systemic symptoms (DRESS), erythema multiforme (EM), or acute generalized exanthematous pustulosis (AGEP).

Rash with appearance of significant systemic signs or symptoms that are new and are considered related to the onset and/or progression of rash should be considered to be grade 3.

**Grade 4, life-threatening:** Diagnosis of generalized bullous eruption, Stevens-Johnson syndrome (SJS), or toxic epidermal necrolysis (TEN).

Determination of seriousness of skin rash events will follow the standard International Conference on Harmonisation (ICH) criteria for serious adverse events as described in Section 12.1.1.

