### **9.3.1.1.3.2. Management of Grade 3 Rash**

General recommendations: For subjects experiencing a grade 3 rash, the same general recommendations as for subjects experiencing grade 1 and grade 2 rashes apply.

Treatment discontinuation: In subjects experiencing a grade 3 rash, telaprevir should be discontinued immediately and permanently. If the rash does not improve, symptomatically or objectively, within 7 days following telaprevir discontinuation, RBV use should also be interrupted. Interruption of RBV dosing may be done sooner if the subject's rash worsens despite discontinuation of telaprevir. Peg-IFN-alfa may be continued unless interruption is medically indicated. The investigator may discontinue telaprevir, Peg-IFN-alfa, and RBV simultaneously if clinically indicated.

However, any subject diagnosed with or suspected to have DRESS, EM, or AGEP must have telaprevir, Peg-IFN-alfa, and RBV discontinued immediately and permanently.

Resumption of treatment: telaprevir dosing cannot be restarted after having been discontinued due to grade 3 rash. Peg-IFN-alfa and/or RBV may be restarted, if interrupted due to grade 3 rash, if there is improvement in the rash within 14 days following the interruption. RBV monotherapy is not allowed; therefore, if Peg-IFN-alfa and RBV dosing are interrupted and RBV is restarted, Peg-IFN-alfa must also be restarted. Please note that any subject who discontinues treatment due to DRESS, EM, or AGEP should not resume telaprevir, Peg-IFN-alfa, or RBV.

Management: The sponsor's physician responsible for the early access program should be notified immediately of any subject who is diagnosed with or suspected to have DRESS, EM, or AGEP. The rash pages in the CRF must be completed.

Referral to a dermatologist is recommended for all grade 3 rashes. The following laboratory tests are mandatory: the hematology tests (with differential) described in Section 9.3, ALT, AST, and creatinine. Any additional or subsequent laboratory testing should be performed as needed, eg, if rash is worsening or if significant laboratory abnormalities that are identified, require monitoring.

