### **9.3.1.1.3.3. Management of Grade 4 Rash**

General recommendations: For subjects experiencing a grade 4 rash, the same general recommendations as for subjects experiencing grade 1, 2, and 3 rashes apply.

Treatment discontinuation: Subjects diagnosed with or suspected to have a skin rash that is considered life-threatening (grade 4 rash), including SJS and TEN, must have telaprevir, Peg-IFN-alfa, and RBV discontinued immediately and permanently.

Resumption of treatment: Any subject who discontinues telaprevir, Peg-IFN-alfa, and RBV due to a grade 4 rash cannot resume treatment.

Management: The sponsor's physician responsible for the early access program should be notified immediately of any subject who is diagnosed with or suspected to have a skin rash that is considered life-threatening (grade 4 rash), including SJS and TEN. The rash pages in the CRF must be completed.

Referral to a dermatologist is recommended for all grade 4 rashes. The following laboratory tests are mandatory: the hematology tests (with differential) described in Section 9.3, ALT, AST, and creatinine. Any additional or subsequent laboratory testing should be performed as needed, eg, if rash is worsening or if significant laboratory abnormalities that are identified, require monitoring.

Close clinical follow-up and appropriate medical intervention should be instituted. Daily follow up, in person or by telephone, to monitor for progression of the event may be necessary from the onset of the event until improvement is observed. Additional visits should be performed (eg, each week or more often, as clinically appropriate). All subjects should be followed until rash has resolved completely.

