### **10.2. Discontinuation of Treatment**

If a subject's study treatment (telaprevir) must be discontinued before the end of the treatment regimen, this will not result in automatic withdrawal of the subject from the early access program.

A subject's treatment (telaprevir, Peg-IFN-alfa, RBV) may be discontinued if:

1. an serious adverse event occurs  
(Note: treatment must be discontinued for skin reactions considered serious adverse events, as described in the table below);
2. they fail to comply with the protocol requirements or fail to cooperate with the investigator.

A subject's treatment with telaprevir may be permanently discontinued if a subject develops a medical condition that requires concomitant therapy with a prohibited drug listed in Section 8.

Subjects must discontinue telaprevir and Peg-IFN-alfa/RBV or have their treatment modified for the reasons included in the table below.

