| DRESS, EM, and AGEP                                                                                                                                                                                                    | 
 
• Permanently discontinue telaprevir, Peg-IFN-alfa, and RBV immediately.
 
                                                                                                                                                                                                                                                                                                                                                                                                                                                                          |
| Grade 4 rash (ie, skin rash that is considered life-threatening), including SJS and TEN                                                                                                                                | 
 
• Permanently discontinue telaprevir, Peg-IFN-alfa, and RBV immediately.
 
                                                                                                                                                                                                                                                                                                                                                                                                                                                                          |
| Anemia (please also refer to Section 9.3.1.2)                                                                                                                                                                          | 
 
• The investigator should consider adjusting the RBV dose, per the product labelling of RBV.
 
• If RBV is permanently discontinued for the management of anemia, telaprevir must also be permanently discontinued.
 
                                                                                                                                                                                                                                                                                                                        |

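### Protocol Section 9.3.1.1.1 requires consulting the monitor before any action when rash grade is in doubt, without excepting the immediate stops that Sections 9.3.1.1.3.2 and 9.3.1.1.3.3 require on suspicion alone

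*Protocol*

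**What the plan says.** Section 9.3.1.1.1 sets a protocol-specific rash scale and adds a rule for uncertain cases: "If there is any doubt about severity grading of a rash event, the investigator must consult with the monitor before taking any action". Neither that sentence nor the grade definitions after it contain an exception.

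The management sections set immediate stops that need only suspicion. Section 9.3.1.1.3.2: "However, any subject diagnosed with or suspected to have DRESS, EM, or AGEP must have telaprevir, Peg-IFN-alfa, and RBV discontinued immediately and permanently". Section 9.3.1.1.3.3 applies the same action to this group: "Subjects diagnosed with or suspected to have a skin rash that is considered life-threatening (grade 4 rash), including SJS and TEN". For both groups, the sponsor's physician responsible for the program should be notified immediately. That is a notification; approval beforehand is not asked for.

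The table in Section 10.2 gives the action for DRESS, EM and AGEP, and again for grade 4 rash: "Permanently discontinue telaprevir, Peg-IFN-alfa, and RBV immediately". Its lead-in makes the table binding: "Subjects must discontinue telaprevir and Peg-IFN-alfa/RBV or have their treatment modified for the reasons included in the table below". These rows name the conditions and do not mention suspected cases. They contain no consultation step.

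**The concern.** Two instructions, both worded as obligations, can apply to the same subject at the same moment. One says to consult before doing anything; the other says to stop three drugs at once. The conditions concerned are among the most dangerous skin reactions the protocol names.

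A cautious site has a reason to take the consult-first rule literally, because stopping cannot be undone. Telaprevir may not be restarted once discontinued for safety, and a subject stopped for DRESS, EM, AGEP or grade 4 rash may not resume any of the three drugs. At stake is a possible delay to a stop that the protocol itself calls immediate. The program is multinational, plans about 3,000 subjects and treats rash as an event of special interest, so sites should not have to work out the order of precedence themselves.

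**Working it through.** No arithmetic applies. The check is whether both rules can be triggered together and, if so, whether any text ranks them.

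**Step 1: triggers and actions.**

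| Section | Trigger | Required action |
|---|---|---|
| 9.3.1.1.1 | Any doubt about rash grade | Consult the monitor before any action |
| 9.3.1.1.3.2 | DRESS, EM or AGEP diagnosed or suspected | Stop all three drugs immediately and permanently |
| 9.3.1.1.3.3 | Grade 4 rash diagnosed or suspected | Stop all three drugs immediately and permanently |
| 10.2, table rows | DRESS, EM and AGEP; grade 4 rash (suspicion not mentioned) | Stop all three drugs immediately and permanently |

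**Step 2: can suspicion coexist with a doubtful grade?** Yes. Grade 4 is defined by a diagnosis of SJS, TEN or generalized bullous eruption. DRESS, EM and AGEP confer grade 3 by diagnosis. The stop rules need suspicion only. A case that is suspected but not diagnosed meets the stop rule while its grade may still be open.

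**Step 3: grade 2 or 3, with DRESS suspected.** Take a morbilliform rash with fever and eosinophilia. The scale allows these signs at grade 2: "Moderate systemic signs and symptoms, such as fever, joint pain, and/or eosinophilia, can be experienced with moderate morbilliform rash". The rash becomes grade 3 if DRESS is diagnosed, or under this criterion: "Rash with appearance of significant systemic signs or symptoms that are new and are considered related to the onset and/or progression of rash". Whether the signs are moderate or significant is a judgment, so doubt is to be expected. At grade 2, Section 9.3.1.1.3.1 asks only that discontinuation be considered if the rash progresses or fails to improve. If DRESS is suspected, Section 9.3.1.1.3.2 requires all three drugs to stop now, while Section 9.3.1.1.1, read literally, requires the call first. This is the clearest collision.

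**Step 4: grade 3 or 4, with SJS or TEN suspected.** Vesicles or bullae, superficial mucosal ulceration, epidermal detachment or target lesions make a rash grade 3 without any diagnosis. Telaprevir is to stop immediately at grade 3 and at grade 4, so its stop does not depend on the doubtful grade. The doubt bears on Peg-IFN-alfa and RBV. At grade 3 the default is stepwise: RBV is interrupted if there is no improvement within 7 days, or sooner on worsening, and Peg-IFN-alfa may continue. However, Sections 9.3.1.1.3.2 and 10.2 also let the investigator stop all three together if clinically indicated. At suspected grade 4, stopping all three is compulsory. The collision here is weaker than in Step 3.

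**Step 5: does any text give precedence?**
- Section 9.3.1.1 says rash management should follow generally accepted medical standards, then adds the protocol's own procedures on top. That does not waive the consult-first rule.
- The contrast that opens the DRESS/EM/AGEP sentence in Section 9.3.1.1.3.2 is with the stepwise grade 3 scheme just before it, and does not refer to the consult-first rule.
- The Section 10.2 rows repeat the immediate stop but do not address suspected cases.
- Section 17.1 excuses prior sponsor contact in emergencies, but for departures from the protocol. The stop is something the protocol requires.

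None of these says that the immediate stop overrides the consultation.

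**The case against.** The strongest reply is that the rules answer different questions. The consult-first rule is in the grading section and, read in context, holds back only actions that depend on the doubtful grade. The DRESS/EM/AGEP stop turns on suspicion of a condition, so grade 2 versus 3 need not be settled first. Section 9.3.1.1.3.3 expressly decides the uncertain grade 4 case, and a specific rule normally prevails over a general one. This is the likely reading in practice, and it is why the point is small. It remains an inference: the consult-first sentence covers any action and has no carve-out.

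Other provisions narrow the overlap, and they stand. Significant new rash-related systemic signs give grade 3 without a diagnosis. All three drugs may be stopped together at grade 3 if clinically indicated. Section 9.3.1.1.3 requires telaprevir to stop permanently for any skin reaction considered a serious adverse event. Section 10.2 provides for stopping telaprevir for other telaprevir safety reasons if the investigator judges that to be in the subject's best interest.

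It can also be said that telaprevir is taken every 8 hours, so a prompt call need not cost a dose. That is fair, but Section 9.3.1.1.1 sets no time limit for the consultation, so the delay cannot be bounded from the document.

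A reader might infer more than the text supports:
- That sites are told in general to postpone stopping for severe rash. They are not: the conflict needs both a doubtful grade and one of the named suspicions.
- That Peg-IFN-alfa and RBV must continue at grade 3 until 7 days have passed. The option to stop all three simultaneously contradicts this.
- That the Section 10.2 rows collide directly with the consult-first rule in suspected cases. They do not mention suspicion.
- That the monitor is the wrong person to ask. Section 12.4 puts the safety contacts in a separate document, so this cannot be judged.

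**Conclusion.** The point holds as a minor wording conflict on subject safety. When DRESS, EM, AGEP or a grade 4 rash is suspected and the grade is still in doubt, Section 9.3.1.1.1 and the management sections give incompatible mandatory instructions, and the protocol does not rank them. The clearest instance is suspected DRESS with a rash between grades 2 and 3.

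This rests on reading the consult-first sentence as written. If investigators let the specific stop rules prevail, as most probably would, there is no practical delay. The protocol gives neither a rate for such cases nor a time for the consultation, so no number of subjects and no length of delay is claimed. A count of the drugs involved would not measure harm and is not offered as one. Nor does the text support inferring a bias in the safety summaries: no effect on any estimate, table or sample-size statement has been shown.

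**What to change.** Add one sentence to Section 9.3.1.1.1: consultation on rash grade must not delay the immediate discontinuations required in Sections 9.3.1.1.3.2, 9.3.1.1.3.3 and 10.2, and runs in parallel with the immediate notification of the sponsor's responsible physician already required in the two management sections.

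The cost is one sentence by protocol amendment, with the usual ethics and regulatory steps. Data collection, sample size and analysis do not change.

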**For rash, all grades will be recorded on the rash pages in the CRF.**

**Grade 1, mild:** Rash is defined as a localized skin eruption and/or a skin eruption with a limited distribution (eg, up to several isolated sites on the body), with or without associated pruritus. A mild rash will have no target lesions, no signs of systemic involvement, and no involvement of mucous membranes or signs of epidermal detachment.

**Grade 2, moderate:** Rash is defined as a diffuse skin eruption involving up to approximately 50% of the body surface area, with or without superficial skin peeling and/or pruritus. Mucosal inflammation without ulceration may be present. Note that mucosal conditions that are not related to skin events, such as aphthous ulcers, stomatitis, or oral lichen planus, should be well documented and not considered when the rash is graded. A moderate rash will have no target lesions or signs of epidermal detachment. Moderate systemic signs and symptoms, such as fever, joint pain, and/or eosinophilia, can be experienced with moderate morbilliform rash. Therefore the type of rash and a thorough assessment of the degree of any systemic signs and their temporal relation to the onset and/or its progression are necessary for rash grading.

**Grade 3, severe:** Rash is defined as a generalized rash involving over 50% of the body surface area, or rash presenting with any of the following characteristics:

- rash with vesicles or bullae;
- superficial ulceration of mucous membranes;
- epidermal detachment (full thickness epidermal necrosis and separation of epidermis from underlying dermis);
- atypical or typical target lesions;
- palpable purpura/non-blanching erythema;
- diagnosis of drug-related eosinophilia with systemic symptoms (DRESS), erythema multiforme (EM), or acute generalized exanthematous pustulosis (AGEP).

Rash with appearance of significant systemic signs or symptoms that are new and are considered related to the onset and/or progression of rash should be considered to be grade 3.

**Grade 4, life-threatening:** Diagnosis of generalized bullous eruption, Stevens-Johnson syndrome (SJS), or toxic epidermal necrolysis (TEN).

Determination of seriousness of skin rash events will follow the standard International Conference on Harmonisation (ICH) criteria for serious adverse events as described in Section 12.1.1.

